### Data management

Each subject will receive a unique identification code when they are included. All data will be collected and stored anonymously and linked to this code. Data will be collected on a paper case report form and paper questionnaires. The data will then be digitized by a trained research assistant and will be verified by the coordinating researcher before analysis. Trial conduct and a sample of the data will also be verified by an independent research monitor during and at the end of the study, and at two time-points during the study. Data from the semi-structured interviews will be recorded using a voice recorder and saved in a password-protected folder, while regular back-ups will be made to a password-protected external hard drive. The recordings will be deleted from the voice recorder immediately after they have been saved on the computer and external hard-drive.

### Sample size

Sample size was calculated in G*power 3.1.9.2 and was based on the primary outcome of this study, difference between means on balance measured with the Mini-BESTest at T_1_. The effect size *d* (0.61) was calculated based on values from an article with a similar study population and an intervention aimed at improving dynamic balance control [56]. We assumed that our control group would remain stable as they receive no extra training aimed at balance improvement. Sample size was based on a one-tailed independent samples t-test, an α of 0.05, power (1-β) of 0.80 and allocation ratio of 1. This results in a required sample size of *n* = 72. Accounting for an expected loss to follow-up of 10%, the final sample size is *n* = 80. Sample size was estimated conservatively, making no assumptions about the correlation between predictors (group allocation and baseline score) added into the model and the outcome variable.

For the purpose of investigating the acceptability of the PBT protocol, a sub-sample from the intervention group will be included. The sample size will be based on the concept of theoretical saturation as described by Glaser & Strauss [57]. If there are two consecutive interviews that provide no new information, no new interviews will be planned. We expect to include approximately 15 subjects for the interviews.

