### Statistical analysis

Data will be analyzed using the Statistical Package for the Social Sciences (SPSS) version 23.0 (SPSS, Chicago, Ill., USA). Descriptive statistics will be used to explore the data and will be presented in tables and figures. Data will be displayed as mean and standard deviation (SD) or as median and interquartile range (IQR), depending on normal distribution of the data. Categorical data will be summarized by frequency (n) or percentage (%). Data will be analyzed on an intention-to-treat basis; missing data will be imputed using multiple imputation. In all statistical analyses, statistical significance will be set at *p* < 0.05. Data-analysis will be performed by a researcher who is blinded to the group allocation.

Primary analysis will test whether there is a significant difference in balance, as measured with the Mini-BESTest, between the control- and intervention groups at T_1_. This will be analyzed using multiple linear regression. Based on the randomization, no between-group differences in variables are expected. However, if there are differences at baseline (based on qualitative appraisal of the baseline table), these factors will be entered into the model. The secondary study parameter ‘fear of falling’ will be analyzed using the same method. The incidence of falls will be analyzed using generalized linear regression with a link function appropriate for the number of falls, using the mean number of retrospective and prospective falls per person-time unit.

A longitudinal analysis will be performed as a secondary, more explorative analysis of balance (Mini-BESTest) and fear of falling (FES-I) over time. A linear mixed effect model will be used to assess the treatment effects, since this model uses all available data, accounts for missing data using a likelihood based method - where missingness at random (MAR) is assumed - and takes the correlation between repeated measurements within a subject into account. The fixed part of the model consists of time, time*treatment, and other covariates that are related to the outcome (power gain) and/or to the missingness (to ensure MAR). The treatment factor, indicating the different treatment groups, is not included, since no group effect is assumed at baseline due to randomization. As for the random part of the model, an unstructured covariance structure is assumed for the repeated measures.

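### The trial is sized on a one-tailed test but its analysis names no direction; read as two-sided, unadjusted power is about 72%, not the stated 80%

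*Protocol article*

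**What the plan says.** The Sample size section of the protocol article bases the calculation on the difference in mean Mini-BESTest at T1. It says "Sample size was based on a one-tailed independent samples t-test", with "an α of 0.05, power (1-β) of 0.80 and allocation ratio of 1". The effect size is taken from a published study: "The effect size *d* (0.61) was calculated based on values from an article with a similar study population". The outcome is "This results in a required sample size of *n* = 72", and then "Accounting for an expected loss to follow-up of 10%, the final sample size is *n* = 80". The section adds a remark on adjustment: "Sample size was estimated conservatively, making no assumptions about the correlation between predictors (group allocation and baseline score") and the outcome.

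The Statistical analysis section says "Primary analysis will test whether there is a significant difference in balance" between the two groups at T1, using multiple linear regression. On the threshold it says "In all statistical analyses, statistical significance will be set at" p < 0.05. It names no direction and no one-tailed test. Baseline variables enter the model only if an informal look at the baseline table suggests that the groups differ.

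**The concern.** The calculation puts the whole 0.05 in one tail. The analysis section describes a test for a difference at p < 0.05, and the ordinary regression p-value for a group coefficient is two-sided. The test that was powered and the test that is described therefore do not match.

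Two things are at stake. First, the 80% power on the primary outcome is not delivered for an unadjusted two-sided test, so the type II error at d = 0.61 would be about 28% rather than 20%. Second, if sidedness is not fixed in advance, a two-sided p-value between 0.05 and 0.10 in favour of the intervention could be called significant or not according to a choice made after seeing it.

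The calculation is also described as conservative. That is true of ignoring the baseline correlation, but the one-tailed choice works in the opposite direction.

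**Working it through.** **Inputs.** From Sample size: d = 0.61, α = 0.05 one-tailed, power 0.80, allocation 1:1, 72 evaluable (36 per group), 10% loss, 80 randomised. From Statistical analysis: p < 0.05, no direction. The baseline-T1 correlation r is not given, so every value of r below is an assumption.

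**Method.** Exact power of the two-sample t-test with n per group: degrees of freedom 2n − 2 and noncentrality δ = d × √(n/2). One-tailed power is P(T > t at 0.95). Two-sided power is P(|T| > t at 0.975). T is noncentral t.

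**1. The plan's own figure.**
- n = 34: δ = 0.61 × √17 = 2.515, df = 66, critical value 1.668, one-tailed power 80.1%.
- n = 33: one-tailed power 79.0%.
- The stated inputs therefore need 34 per group, **68 in total, not 72**.
- Rounding does not close the gap: an unrounded d between 0.605 and 0.615 gives 68 to 70.
- Sidedness does not explain it either, because the two-sided total is 88 (step 3).
- A total of 72 needs d of about 0.592 to 0.600. Alternatively, it fits a rank-test efficiency correction: 34 × π/3 = 35.6, so 36 per group. That is not the test named.
- The loss step is right: 72 / 0.9 = 80.

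**2. Power at the planned size, unadjusted, d = 0.61.**

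| Evaluable | δ | One-tailed power | Two-sided power |
|---|---|---|---|
| 72 (36 per group) | 0.61 × √18 = 2.588 | 82.1% | **72.3%** |
| 80 (40 per group) | 0.61 × √20 = 2.728 | 85.5% | **76.9%** |

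With 36 per group (df = 70), the critical value moves from 1.667 one-tailed to 1.994 two-sided. That shift is the whole loss of power.

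**3. What 80% two-sided would need, unadjusted.** 43 per group gives 79.8% and 44 gives 80.8%, so 88 evaluable. Then 88 / 0.9 = 97.8, so 98 randomised. With 36 per group, the difference detectable with 80% two-sided power is d = 0.67.

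**4. Effect of adjusting for the baseline score.** Adjustment shrinks the residual SD by √(1 − r²), so the effective d is 0.61 / √(1 − r²). Two-sided power with 36 per group:

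| Assumed r | Effective d | Power |
|---|---|---|
| 0 | 0.610 | 72.3% |
| 0.3 | 0.639 | 76.3% |
| 0.4 | 0.666 | 79.5% |
| 0.5 | 0.704 | 83.8% |
| 0.6 | 0.763 | 89.1% |

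Power reaches 80% at r of about 0.41. The gain can be counted on only if the baseline score is always in the model. Sample size speaks of the baseline score as a predictor in the model, whereas Statistical analysis adds baseline factors only on apparent imbalance. The two sections do not agree on this.

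**The case against.** The strongest reply is that the protocol never uses the term two-sided. The only sidedness it states is one-tailed, and it states that openly in a trial described as a superiority design. If the regression coefficient were tested one-sided at 0.05, the sections would agree and power would be 82%. It is fair that the two-sided reading is an inference. But a superiority design does not settle sidedness, and the analysis section describes a difference without a direction. If a one-sided test was meant, that section needed to say so and justify it.

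A second reply is that the planned analysis is a regression, not a t-test, and that ignoring the baseline correlation was deliberately cautious. This also stands in part. A reader might infer that the trial simply has 72% power, but the documents do not support that as a flat statement. The 72% is for an unadjusted two-sided comparison, and with adjustment power could exceed 80%. Equally, 80% cannot be claimed, since no correlation is given and adjustment is conditional.

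A reader might also infer from 68 against 72 that the trial is too small by its own reckoning. The reverse is true: under the stated one-tailed test, 72 gives slightly more power than stated. The gap is four subjects and is a reporting slip.

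**Conclusion.** The concern holds as a mismatch between the powered test and the described test. On the natural two-sided reading, with d = 0.61 and no adjustment, power is 72% with 72 evaluable and 77% with all 80. The stated 80% applies to a one-tailed test, for which 72 evaluable give 82%. With the baseline score always in the model, two-sided power would run from about 76% (r = 0.3) to 84% (r = 0.5), crossing 80% near r = 0.41; these correlations are assumptions. The conclusion rests on reading an unlabelled p < 0.05 for a difference as two-sided. The failure of 72 to reproduce from the stated inputs is separate and minor.

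**What to change.** Four changes of wording, none of which needs more patients:

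1. State in Statistical analysis that the primary test is two-sided at 0.05.
2. Make baseline Mini-BESTest a fixed covariate in the primary regression, whatever the baseline table shows, so that the two sections agree and the gain in power can be relied on.
3. Restate the power as about 72% for an unadjusted two-sided comparison with 72 evaluable subjects and d = 0.61. Add the range under adjustment, with each correlation labelled as assumed (for example 76% at 0.3, 84% at 0.5).
4. Correct whichever of d, the test or the total produced 72: 68 for d = 0.61 as written, or the unrounded d or the test actually used.

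The changes should be made before any unblinded analysis. The cost is that the stated power becomes less favourable.

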### Statistical analysis

Data will be analyzed using the Statistical Package for the Social Sciences (SPSS) version 23.0 (SPSS, Chicago, Ill., USA). Descriptive statistics will be used to explore the data and will be presented in tables and figures. Data will be displayed as mean and standard deviation (SD) or as median and interquartile range (IQR), depending on normal distribution of the data. Categorical data will be summarized by frequency (n) or percentage (%). Data will be analyzed on an intention-to-treat basis; missing data will be imputed using multiple imputation. In all statistical analyses, statistical significance will be set at *p* < 0.05. Data-analysis will be performed by a researcher who is blinded to the group allocation.

Primary analysis will test whether there is a significant difference in balance, as measured with the Mini-BESTest, between the control- and intervention groups at T_1_. This will be analyzed using multiple linear regression. Based on the randomization, no between-group differences in variables are expected. However, if there are differences at baseline (based on qualitative appraisal of the baseline table), these factors will be entered into the model. The secondary study parameter ‘fear of falling’ will be analyzed using the same method. The incidence of falls will be analyzed using generalized linear regression with a link function appropriate for the number of falls, using the mean number of retrospective and prospective falls per person-time unit.

A longitudinal analysis will be performed as a secondary, more explorative analysis of balance (Mini-BESTest) and fear of falling (FES-I) over time. A linear mixed effect model will be used to assess the treatment effects, since this model uses all available data, accounts for missing data using a likelihood based method - where missingness at random (MAR) is assumed - and takes the correlation between repeated measurements within a subject into account. The fixed part of the model consists of time, time*treatment, and other covariates that are related to the outcome (power gain) and/or to the missingness (to ensure MAR). The treatment factor, indicating the different treatment groups, is not included, since no group effect is assumed at baseline due to randomization. As for the random part of the model, an unstructured covariance structure is assumed for the repeated measures.

For the analysis of the qualitative data, the interviews will be transcribed verbatim. All transcriptions will be double-checked by a second researcher. A summary of the interview will be sent to the subject, so they have the opportunity to check the information and provide feedback. A deductive content analysis based on the theoretical framework of acceptability will be performed on the data using NVivo software, version 12 (QRS International). The transcripts will be coded independently by two researchers. After this, any differences in coding will be discussed. A third researcher will be available to reach consensus if necessary. An unstructured categorization matrix will be utilized, so topics that do not fit the initial framework can be added based on inductive content analysis [58]. If new topics arise during data collection, they will be added to the interview guide.

Circumstances and consequences of fall incidents, whether injurious or not, will be reported qualitatively, and using descriptive statistics.

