### Recruitment, randomization, blinding and treatment allocation

Eligible patients will be informed about this study by their medical doctor when they visit the outpatient clinic of the MUMC+. If patients are interested in the study, they will receive written information and will be asked for their permission to be phoned by the investigators. Patients are given the opportunity to read the study information at home and will be phoned by the investigators 3 to 7 days later. If a patient wants to participate, an appointment will be scheduled to visit the MUMC+ department of physical therapy. During this visit, any remaining questions will be answered and written informed consent will be obtained.

After this, the investigator will check the eligibility criteria. If the subject meets the criteria, baseline measurements will be performed. When these have been completed, the subjects will be randomized to the intervention- or control group. This will be done using a 1:1 ratio stratified block randomization (block sizes 2 and 4 will be randomized). Randomization will be stratified based on sex (male versus female) and number of falls during the past year (1 versus 2 or more). This stratification will result in four different strata. The randomization sequence will be generated using an online random number generator. The allocation will be concealed by using sequentially numbered, sealed opaque envelopes. The person preparing the allocation concealment mechanism will be a different person than the one enrolling the subjects and assigning them to a group. The allocation sequence list will be kept in a locked drawer, which can be accessed only by the principal investigator.

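### Covariates for the primary regression are picked by eye from the baseline table, so the primary model is not fixed in advance and the place of the baseline score is left unclear

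*Protocol article*

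**What the plan says.** Under Statistical analysis, the article compares the groups on the Mini-BESTest at T1 and states: "This will be analyzed using multiple linear regression". No covariate is named. The article expects no group differences after randomisation, but adds that "if there are differences at baseline (based on qualitative appraisal of the baseline table), these factors will be entered into the model". Fear of falling follows suit: "The secondary study parameter ‘fear of falling’ will be analyzed using the same method". The same section says: "Data-analysis will be performed by a researcher who is blinded to the group allocation".

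Under Sample size, the calculation is called conservative because it was done "making no assumptions about the correlation between predictors (group allocation and baseline score) added into the model and the outcome variable". Here the baseline score appears as a predictor in the model, with no condition attached.

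Under Recruitment, randomization, blinding and treatment allocation, the design is a "1:1 ratio stratified block randomization (block sizes 2 and 4 will be randomized"), and "Randomization will be stratified based on sex (male versus female) and number of falls during the past year (1 versus 2 or more"). Neither stratification factor is mentioned in the primary model.

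**The concern.** The article does not simply leave the covariate list to a later document. It states a rule, and the rule is a poor one, for three reasons.

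- **It is not reproducible.** With no threshold and no candidate list, two analysts could read the same baseline table differently and report different primary estimates and p-values.
- **It selects on the wrong property.** A covariate earns its place by predicting the outcome, whether or not it happens to be imbalanced. The article's own secondary mixed model follows that principle: it admits covariates for their relation to the outcome or to missingness.
- **It works against the stratification factors.** Sex and prior-year falls are balanced by design, so a rule triggered by imbalance will seldom choose them. A stratified design analysed without its strata gives standard errors that are too wide when those factors are prognostic.

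The baseline Mini-BESTest score is likely to be the most prognostic covariate, and the text does not settle whether it is always in the model or enters only if the groups look different on it. Precision of the primary result is at stake in a trial of 80 people.

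**Working it through.** **Inputs from the article (Sample size):** d = 0.61, one-tailed t-test, α = 0.05, power 0.80, 1:1 allocation, 72 required, 10% loss, 80 recruited.

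**Inputs assumed, because the article gives none:** baseline–T1 correlation r (0.3 to 0.7 shown), a trigger of 0.25 SD standing in for the visual appraisal, and two-sided testing at 5% (the analysis section does not state sidedness).

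**Step 1: the plan's own figure.** A one-tailed t-test with d = 0.61 needs 34 per arm, 68 in total (exact power 80.1%). The stated 72 is slightly larger; it results if d is 0.595 to 0.60. The dropout step reproduces: 72 / 0.90 = 80. The gap between 68 and 72 does not affect this point. I use 72 analysed, 36 per arm.

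**Step 2: power with a fixed model.** The noncentrality parameter is d × √(n/2) unadjusted and d / √(1 − r²) × √(n/2) with the baseline score always in; √(36/2) = 4.243.

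- Unadjusted: 0.61 × 4.243 = 2.59, two-sided power 72% (one-sided 82%).
- r = 0.3: 0.61 / 0.954 × 4.243 = 2.71, power 76%.
- r = 0.5: 0.61 / 0.866 × 4.243 = 2.99, power 84%.
- r = 0.7: 0.61 / 0.714 × 4.243 = 3.62, power 95%.

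Simulation of the always-adjusted model gives 83% (r = 0.5) and 94% (r = 0.7), with type I error close to 5%.

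**Step 3: how often the rule would leave the baseline score out.** The standardised baseline difference has standard error √(2/36) = 0.236. A trigger of 0.25 lies 0.25 / 0.236 = 1.06 standard errors from zero, so the score would be left out in about 70% of trials.

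**Step 4: the rule under the two readings.** Simulated at 36 per arm, d = 0.61, two-sided 5%, trigger 0.25 SD. Ranges span runs with the baseline score as the only candidate and runs with six weaker covariates added.

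| Reading | Power, r = 0.5 | Power, r = 0.7 | Type I error, r = 0.5 | Type I error, r = 0.7 |
|---|---|---|---|---|
| Baseline score always in, no selection | 83% | 94% | about 5% | about 5% |
| Baseline score subject to the rule | 75–77% | 81–82% | 3.3–3.7% | 2.1–2.5% |
| Baseline score always in, other factors by the rule | 82–83% | 94–95% | 4.1–4.8% | 3.6–4.4% |

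At r = 0.3, with the baseline score as sole candidate, the rule gives 73% power against 76%, and type I error 4.6%.

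The type I error is low because the unadjusted analysis is kept exactly when the baseline means are close. In those trials the estimate varies less than its standard error says.

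**Step 5: leaving out a stratification factor.** In a simulation with one two-level factor exactly balanced across arms and explaining 10% or 20% of outcome variance (assumed), omitting it gives type I error 3.7% or 2.8%. Including it gives 4.8% or 5.0%.

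**The case against.** The strongest reply has five parts.

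- **The two sections can be read together.** The sample-size text puts the baseline score in the model, and multiple regression already implies more than one predictor. The rule says what is added; it never says a balanced baseline score is dropped. A reader might infer a flat contradiction, or take the power loss as established. The documents support neither. The analysis section does not state the reconciling reading, however, so the ambiguity stands.
- **The analyst is blinded to allocation.** A baseline table with coded arms can be appraised under blinding and contains no T1 results. A reader might infer that the model could be chosen on its outcome. With free choice between adjusted and unadjusted results, type I error would be 7.4% (r = 0.5) or 8.3% (r = 0.7), but nothing in the article describes such a choice. Blinding limits this risk; it does not make the model pre-specified.
- **The error is conservative.** Applied mechanically, the rule does not inflate false positives, and randomisation protects the estimate from systematic bias. Both statements stand.
- **Planned power is met anyway.** On the one-tailed basis of the sample-size section, unadjusted power is already 82% at 36 per arm. That is correct, but it is no reason to forgo precision that costs nothing.
- **An article may leave its covariate list to the analysis plan.** True, and the article does not exclude sex or prior falls. The point rests on the rule it does state.

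**Conclusion.** The point holds as a badly fixed rule for the primary model. The harm is a model that is not settled in advance, conservative error bars and possibly lost power. It is not bias or false-positive inflation.

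The size depends on the reading that the article leaves open. If the baseline score is subject to the appraisal, the loss is about 6 to 8 percentage points of two-sided power at r = 0.5 (83% against 75–77%) and about 12 to 13 at r = 0.7 (94% against 81–82%). If the baseline score is always in, almost none of that loss remains, and type I error is about 4–5%. The correlations, the 0.25 SD trigger, the strength of the weaker covariates and the variance explained by a stratification factor are all assumptions. The defect in the rule itself depends on none of them.

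**What to change.** Fix the primary model in advance: Mini-BESTest at T1 on treatment, baseline Mini-BESTest, sex, and prior-year falls (1 versus 2 or more), whatever the baseline table shows. Use the same form for FES-I, with baseline FES-I in place of the baseline Mini-BESTest. Make the Sample size and Statistical analysis sections agree that the baseline score is always included. Delete the appraisal rule, or keep it only as a labelled sensitivity analysis.

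The cost is wording. The Mini-BESTest, FES-I and fall history are already recorded at baseline, and sex is needed for the stratification. With 72 analysed, the five-parameter model leaves 72 − 5 = 67 residual degrees of freedom, against 70 unadjusted. The change should be made before the blinded analyst sees the baseline table by arm.
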